### Safety

Adverse event monitoring will begin after participants have been randomized and will last 24 weeks. All adverse events related to the intervention will be recorded and reported according to the standardized guidelines for reportable events. The grading will be done using the Common Terminology Criteria for Adverse Events by the US National Cancer Institute. Patients will be informed about contraindication for exercise training and will be advised to stop exercising when they feel pain or other symptoms.

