## Methods/design

### Study design

The IRENE-G study is a 24-week prospective, randomized, controlled, intervention trial with a two-armed parallel design and 1:1 allocation ratio of GvHD patients treated with systemic steroids.

The study examines and compares the effects of a supervised resistance exercise intervention and a nutritional optimization program (experimental group) against a nutritional optimization program only (control group) on physical performance in GvHD patients treated with steroids. The investigators hypothesize that both groups will benefit with regard to physical performance after 24-weeks, however, the authors assume that the effect will be significantly greater in the experimental group compared to the control group. Moreover, the investigators hypothesize that the experimental group will have lower levels of fatigue, less perceived GvHD symptom burden, a higher perceived quality of life, better muscle strength values and a higher vastus lateralis muscle volume, a better nutritional status as well as a better submaximal endurance capacity compared to the control group.

The flow through the IRENE-G study is presented in Fig. 1. The research will be conducted at a single site (University Hospital Heidelberg, Germany). Upon written informed consent, eligible patients will be randomly assigned to the experimental or control group. Patients in the experimental group will take part in a 24-week supervised resistance exercise program and a nutritional optimization program. The moderate-to-high intensity resistance exercise sessions will be performed for a duration of 60 min two times a week. Patients in the control group receive nutritional optimization only. The interventions will start directly after the completion of the baseline measurements (t0). Further assessments will take place 8 weeks (t1), 16 weeks (t2), and 24 weeks (t3, primary endpoint assessment) after baseline assessment. A follow-up assessment (t4) is planned 48 weeks after baseline. All assessment points are embedded into medical care/ outpatient visits.

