### Study outcomes

An overview of the outcome measures used in the IRENE-G study, including the time of data collection can be viewed in Table 1. The analysis metrics of interest are difference between the treatment arms throughout the study and change from baseline to t3.

**Table 1 Tab1:** Study outcomes, instruments and assessment points

Outcomes	Instrument	t0	t1	t2	t3	t4
*Primary endpoint*						
Physical performance	Short Physical Performance Battery	x	x	x	x	x
*Secondary endpoints*						
Muscle strength	Hand-grip test, Hand-held Dynamometer	x	x	x	x	x
Muscle volume	Ultrasound	x			x	x
Submaximal endurance capacity	6 minutes walk test	x	x	x	x	x
Nutritional status	NRS 2002, hand- grip test, serum albumin, total protein levels	x	x	x	x	x
Quality of life	EORTC QLQ-C30/ HDC-29	x	x	x	x	x
Fatigue	EORTC QLQ-FA 12	x	x	x	x	x
GvHD Symptom burden	Modified 7-day Lee cGvHD Symptom Scale	x	x	x	x	x
Performance status	Karnofsky Performance Scale	x	x	x	x	x
*Others*						
Socio-demographic factors	Sex, age, marital status, family and living situation, education, employment status and smoking behavior	x			x	x
Physical activity (history)	Physical activity pre-diagnosis and during the intervention	x	x	x	x	x
Amnestic variables, medical history	Date of diagnosis, subtype of disease, remission status, conditioning regime, history of therapy, date of allo HSCT transplantation, HLA compatibility and comorbidities will be recorded from medical records	x				
Anthropometric data	Weight, height	Weekly				
Concomitant medication	Medical log	At each medical outpatient visit				
GvHD course	Physician rating	At each medical outpatient visit				
Adverse events	Medical records, reports of the exercise therapists and/or patient	Surveillance throughout the study				
Adherence to the exercise intervention	Self-reported and objective measures (e.g. attendance, exercise log, target intensity) of the intervention arm only	Surveillance throughout the study				

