### Interventions

Both study interventions (nutritional optimization as well as exercise training) will be delivered for a duration of 24 weeks followed by a 6 month follow-up phase. For both arms there are arrangements for ancillary or post-trial care. No special arrangements for compensation for those who suffered harm resulting from trial participation are taken. A decision to discontinue an individual’s intervention will be made jointly within the investigator team if there is concern that the intervention is causing harm. The overall study will be discontinued if the ethic committee decides to terminate the study. During the trial, no specific concomitant care or interventions are prohibited.

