Exercise training is scheduled 2 times a week (separated by at least 48 h) for a total duration of 60 min. The program targets all major muscle groups, however, emphasis will be put on the lower extremities, as they are primarily affected by the GvHD treatment. The focus of the resistance training will be on muscle hypertrophy. The progressive program for participants who will train at facility centers comprises of 6–8 machine-based exercises, each performed in two sets, 12 repetitions at 60–80% of one repetition maximum (1-RM). For participants who train online, the individual training load will be defined during the introductory training session with the aim of choosing a load which to perform two times 12 repetitions. Patients will be coached in correct techniques for each exercise. Resting time between sets will be 1–2 min, and contractions will be performed at moderate velocities. The exercise intensity will be continuously adapted throughout the 24 weeks. The training is progressive in terms of weight increase to the next machine weight level (at least by 5%) after successfully completing two sets of an exercise with 12 repetitions in three consecutive exercise sessions. If deteriorations occur, the weights will be decreased, if two sets of an exercise within 12 repetitions in two consecutive exercise sessions cannot be attained. Participants will be contacted when 2 session in a row were not joined, without reasoning. Compliance with the exercise program will be determined via self-reported and objective measures such as attendance, exercise logs, target intensity.

Before and after each training session, participants will be asked to complete an exercise log. The physical activity log will be used for exercise monitoring and for adjusting. Moreover, it will be used as a measure of additional physical activity outside of the exercise intervention (such physical activity is not restricted or prohibited). Patients will be asked to report their perceived health status prior and after the training session as well as problem or symptom occurrence related to the exercise program. Further, the performed sets and repetition as well as the perceived exertion of each exercise and discomfort will be recorded. Every 4 weeks patients are instructed to drop off the logs during outpatient visit.

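### The Safety section records adverse events only when related to the intervention, while Table 1 sets no such limit; in an unblinded trial with exercise-arm-only reporting sources, recorded counts may be biased between arms

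*Protocol article*

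**What the plan says.** The Safety section fixes the scope of recording: "All adverse events related to the intervention will be recorded and reported according to the standardized guidelines for reportable events". It fixes the window too: "Adverse event monitoring will begin after participants have been randomized and will last 24 weeks". It does not say who decides that an event is related.

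Table 1 (Study outcomes) has an adverse event row with no relatedness limit. Its sources are "Medical records, reports of the exercise therapists and/or patient" and its timing is "Surveillance throughout the study".

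The Exercise intervention section has participants complete a log before and after each training session. Among other things, the log asks about "problem or symptom occurrence related to the exercise program". Only the experimental arm trains. Recruitment and randomization states that neither participants nor staff are blinded after allocation.

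On study length, the article says "A follow-up assessment (t4) is planned 48 weeks after baseline" and that both interventions "will be delivered for a duration of 24 weeks followed by a 6 month follow-up phase". It also says "The IRENE-G study is a 24-week prospective, randomized, controlled, intervention trial".

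**The concern.** Read naturally, the Safety section makes relatedness a condition for entering the record. Nothing there provides for recording an event that nobody attributes to an intervention. Three features make this a problem in a two-arm comparison.

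- Anyone on the trial staff who attributes an event knows the patient's arm.
- The interventions differ between arms, so the question of relatedness is not the same question in each.
- Two detection channels, the session log and the therapist's report, exist in one arm only.

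Background morbidity is high here. The Background lists bone and muscle damage from steroids, and the Sample size section expects 10% mortality. In such a population, attribution in an individual patient is unreliable, and the randomised contrast in all events is the better evidence. The article itself says that there is no evidence yet on structured exercise in GvHD, and it assumes rather than shows that online training is safe in these patients. It plans no data monitoring committee and no independent auditing, so no other described safeguard would make up for a distorted harm record.

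**Working it through.** The article gives no adverse event rate, so there is no figure to reproduce. The check is a comparison of the stated rules, followed by an illustration on assumed rates.

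**1. Scope.** Safety: events related to the intervention. Table 1: adverse events, no limit, with medical records as one source. The two do not match.

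**2. Detection sources by arm.**

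| Source | Experimental | Control |
|---|---|---|
| Medical records, patient reports (Table 1) | yes | yes |
| Weekly contact about nutrition (Nutritional intervention) | yes | yes |
| Therapist reports (Table 1) | yes | no training, so none |
| Session logs (Exercise intervention) | up to 2 per week × 24 weeks = 48 sessions | no training, so none |

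The figure of 48 is a ceiling that assumes full attendance.

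**3. Effect of the filter (illustration).** Let p be the true share of patients with an event and q the share of these attributed to the intervention. The recorded share is p × q. All values of p and q are assumptions; 56 per arm is from the Sample size section.

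Same true risk in both arms, so the recorded difference is p × (q_exp − q_con) and is entirely false:

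| p | q_exp v q_con | Recorded | Of 56 | False difference |
|---|---|---|---|---|
| 30% | 20% v 10% | 6% v 3% | 3.4 v 1.7 | 3 points |
| 50% | 30% v 10% | 15% v 5% | 8.4 v 2.8 | 10 points |
| 80% | 30% v 5% | 24% v 4% | 13.4 v 2.2 | 20 points |
| 50% | 10% v 10% | 5% v 5% | 2.8 v 2.8 | 0 |

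Opposite direction: if staff attribute less often in the exercise arm, say p = 50% with 5% v 10%, the record shows 0.50 × 0.05 = 2.5% v 0.50 × 0.10 = 5%, a false deficit of 2.5 points.

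Masking: with equal attribution of 10% but true risks of 80% v 50%, the record shows 8% v 5%. A true difference of 30 points appears as 3.

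**4. Window.** If the study runs to t4, 48 − 24 = 24 weeks, or 24/48 = 50%, fall under Table 1 but outside the Safety window. If the study means the 24-week trial, the gap is 0. Table 1 gives exercise adherence the same timing although training lasts 24 weeks, so the shorter reading is open. Under either reading the window is the same for both arms.

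**The case against.** The strongest reply is that the Safety sentence does not say unrelated events are thrown away. Table 1 names medical records, operational detail may sit in a full protocol that is not shown, and harm is neither a primary nor a secondary endpoint but is only to be described. Part of this stands: the article promises no formal comparison of harm, and it does not state that unrelated events are discarded. But the scope is a stated rule, not an omitted detail. It disagrees with Table 1, and a descriptive table by arm will still be read as a comparison.

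A reader might infer more than the article supports:

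- *That all unrelated events, including GvHD flares, are lost.* Table 1 records GvHD course and concomitant medication at each medical outpatient visit and GvHD symptom burden at t0 to t4. None of these is limited to one arm or filtered by relatedness.
- *That the exercise arm is questioned 48 times and the control arm never.* That counts session logs only. Both arms have weekly nutritional contact, and Table 1 accepts patient reports.
- *That control events have nothing to be related to.* Controls receive nutritional optimization, which the Interventions section treats as a study intervention and which can extend to enteral or parenteral nutrition.
- *That the window makes the comparison unfair.* It applies equally to both arms and can only shorten harm follow-up. Whether it contradicts Table 1 depends on what the study is taken to mean.

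**Conclusion.** The point holds in a limited form. The Safety section provides for recording intervention-related events only, which does not agree with Table 1. With no blinding and two reporting channels confined to the exercise arm, the recorded counts may be biased in either direction. It would go too far to say that the arms cannot be compared on harm at all.

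The size is unknown. On the assumed rates above (true risk 30% to 80%, attribution 20% to 30% in the experimental arm v 5% to 10% in the control arm), the false excess is 3 to 20 percentage points. It is zero if attribution and detection are equal, but nothing in the design gives reason to expect that.

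The window is a separate, smaller matter: an ambiguity worth 0 or 24 weeks of harm follow-up. The whole is worth correcting because the remedy is cheap.

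**What to change.** In the Safety section:

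- Record adverse events, at least all serious events and all of CTCAE grade 3 or higher, in both arms whether or not they are thought related.
- Take them from sources common to both arms: medical records, and the same questions asked at the scheduled visits.
- Keep relatedness as a recorded attribute of each event, not a condition of entry.
- Report symptoms from session logs and therapists separately, for the experimental arm only, and keep them out of the between-arm table.

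Separately, state one end of adverse event recording, in weeks, in both the Safety section and Table 1, so that it is clear whether the period up to t4 is covered.

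The cost is more event entries and one case report form page. Records and outpatient visits already exist in both arms. One limit remains: the analysis section evaluates adverse events in the per-protocol population, which could leave out patients who stopped training because of an event. Changing what is recorded does not resolve that, so the analysis set should be reconsidered alongside.

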### Intended statistical analysis

Data of the primary endpoint will be analyzed after study completion, no interim statistical analysis will be conducted. Descriptive statistics will be performed for sociodemographic and clinical variables measures at baseline for both arms. Absolute and relative frequencies will be used for categorical and the mean ± standard deviation (or median and range) will be used for continuous variables. In addition to descriptive evaluation procedures, inferential statistical methods will be used. The primary analysis will be based on an intention-to-treat principle. The authors will use ANCOVA to compare the SPPB changes from baseline to the end of the intervention between the two intervention arms. Standardized effect sizes with 95% confidence intervals will be calculated. For further exploratory analyses further model procedures (e.g. generalized estimating equation) and multiple regressions will be used. The significance level will be set at α = 0.05 (two-sided). Missing data will be dealt with using scoring manuals if present. When clinically and methodological reasonable, multiple imputation will be used. Adverse events will be evaluated descriptively based on the per-protocol population. Statistical analyses will be carried out in cooperation with the Institute for Medical Biometry at the University of Heidelberg. Access to the final dataset will be granted for the statistician and the principal investigators.

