### Sample size

To our knowledge no supervised, progressive moderate-to-high intensity resistance exercise study in a GvHD population treated with systemic steroids with the primary endpoint physical performance measured via the SPPB exists, as of yet. Consequently, the effect size for the primary outcome measure is unknown. The sample size calculation for the present exploratory project is based on a conservative estimation, using a mean standardized effect size of 0.5. To detect a corresponding effect with ANCOVA at a significance level of 5% with a power of 80%, 42 participants per group are required. Based on unpublished data of a previous study of ours, we expect a drop-out rate of 15% and a mortality rate of 10%. Consequently, 56 subjects per group need to be enrolled.

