After the completion of the baseline measurements, patients will be randomly assigned to one of the two arms with a 1:1 allocation, using REDCap (Research Electronic Data Capture) randomization module (automated assignment system) [99, 100]. To avoid imbalance between the arms, block randomization procedure is applied. Stratification factors for the randomization include intensity of conditioning for allo HSCT (reduced-intensity vs myeloablative), haploidentical transplantation (yes vs. no) and type of GvHD (acute vs. chronic). The allocation table has been generated with R [101] by an project-independent employee of the research department based on the given requirements.

Allocation concealment will be ensured, as the randomization module will not release the code until the patient has been recruited into the trial and has completed the baseline assessment. After assignment to one of the arms, neither participants nor staff can be blinded to allocation due to the nature of interventions and staffs’ direct involvement within the intervention program (e.g. training organization, phone calls about participants’ wellbeing).

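### Randomisation is stratified on three factors, but the primary ANCOVA is stated without them; naming them as covariates is a nearly free gain

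*Protocol article*

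**What the plan says.** Under Recruitment and randomization, the protocol article states: "To avoid imbalance between the arms, block randomization procedure is applied". It then lists three two-level factors: "Stratification factors for the randomization include intensity of conditioning for allo HSCT (reduced-intensity vs myeloablative), haploidentical transplantation (yes vs. no) and type of GvHD (acute" versus chronic). Crossed, they give eight strata. The block size is not given.

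Under Intended statistical analysis, the primary analysis follows the intention-to-treat principle, and the comparison is described in one sentence: "The authors will use ANCOVA to compare the SPPB changes from baseline to the end of the intervention between the two intervention arms". No covariate is listed, neither baseline SPPB nor any stratification factor. Generalized estimating equations and multiple regressions are mentioned only for further exploratory analyses. The test level is "The significance level will be set at α = 0.05 (two-sided").

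Under Sample size, a standardised effect of 0.5 is assumed and the calculation also rests on ANCOVA: "To detect a corresponding effect with ANCOVA at a significance level of 5% with a power of 80%, 42 participants per group are required".

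**The concern.** Stratified blocks force the arms to be nearly balanced on the three factors. If those factors predict the outcome, the treatment difference varies less from one randomisation to the next than it would under simple randomisation. A model without the factors does not know this. It keeps their variance in the error term, so the standard error it reports is larger than the true one. The consequences are a test that rejects less often than 5% under the null, an interval that covers more often than 95%, and some loss of power.

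Covariates also matter to this trial's own power claim. The planned 42 per group is reachable at an effect of 0.5 only if some covariate explains about a third of the outcome variance, and the article names none. The authors expect 15% drop-out and 10% mortality, and the Discussion calls the sample size a challenge in this setting, so even a few points of power are worth keeping.

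**Working it through.** **Inputs from the article.** Standardised effect 0.5; two-sided 5% level; 80% power; 42 evaluable per group; 56 enrolled per group; 1:1 allocation; three binary stratification factors; block randomisation.

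**Assumptions (not in the article).** Blocks of 4 within the eight strata; factor prevalences 50%, 15% and 50%; baseline SPPB explains one third of outcome variance; the three factors together explain a share q of what is left after baseline (partial R²), with q = 0, 0.05, 0.10 or 0.20.

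**Step 1: the plan's own figure.** Without covariates, n per group = 2(1.96 + 0.8416)²/0.5² = 62.8, so 63 (64 with the t distribution). To reach 42, the variance must shrink by the factor 42/62.8 = 0.67. This means R² of about 0.33, or a covariate–outcome correlation of about 0.58. The one-third assumption above comes from here. The inflation step reproduces: 42/(1 − 0.25) = 56.

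**Step 2: interval width.** With good balance on the factors, adding them multiplies the standard error by about √(1 − q). Degrees of freedom go from 84 − 3 = 81 to 84 − 6 = 78, which changes the t quantile by only about 0.1%.

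| q | √(1 − q) | Width with factors / without |
|---|---|---|
| 0 | 1.000 | 1.001 |
| 0.05 | 0.975 | 0.975 |
| 0.10 | 0.949 | 0.949 |
| 0.20 | 0.894 | 0.895 |

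**Step 3: analytic power at 42 per group.** The noncentrality is 0.5/√[(2/3)(1 − q)(2/42)].
- Baseline only: 0.5/0.178 = 2.81, power 79.2%.
- With the factors, q = 0: power 79.1%. This is the whole cost if they are not prognostic.
- With the factors, q = 0.05, 0.10 and 0.20: noncentrality 2.88, 2.96 and 3.14, power 81.2%, 83.2% and 87.3%.

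**Step 4: simulation of the stratified design.** 84 patients, 4,000 replicates per scenario. The model always contains baseline and either omits or includes the three factors.

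| q | Type I error, omitted | Null coverage, omitted | Power, omitted | Power, included |
|---|---|---|---|---|
| 0 | 5.1% | 94.9% | 79.1% | 78.8% |
| 0.05 | 4.5% | 95.5% | 79.7% | 80.8% |
| 0.10 | 4.2% | 95.8% | 79.6% | 82.5% |
| 0.20 | 3.7% | 96.3% | 80.2% | 86.1% |

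The power differences are 1.1, 2.9 and 5.9 points for q = 0.05, 0.10 and 0.20. They are smaller than the gaps in step 3 because the stratified design already gives the model without factors a slightly less variable estimate, and because covariates are not perfectly balanced in finite samples. The simulated differences are the relevant ones.

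**Step 5: how firm the type I figures are.** The simulation standard error near 5% is √(0.05 × 0.95/4000) = 0.34 points. Perfect balance would give 2Φ(−1.96/√(1 − q)) = 4.4%, 3.9% and 2.8%; incomplete blocks move the result back towards 5%. A longer run (20,000 replicates, same settings) gave 4.6%, 3.8% and 3.3%. With 112 randomised and a random 25% lost, it gave 4.5%, 4.4% and 3.7%. The pattern is stable, and the figures are good to about half a point. With the factors included, the shorter run gave 4.8%, 5.1% and 6.0%. The last value is simulation noise: the longer run gave 5.2%.

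**The case against.** The strongest objection is that silence is not exclusion. An ANCOVA must have at least one covariate and the article lists none, so the sentence is plainly abbreviated. Covariate lists commonly sit in a full protocol or analysis plan, neither of which is shown, and stratifying and then using ANCOVA are fully compatible. This stands. A reader might infer that the plan leaves the strata out on purpose or prescribes an unadjusted comparison; the article says neither.

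Second, the loss is conditional. A reader might infer that the factors were chosen because they predict SPPB. The article gives only balance between the arms as the reason, and no figure links any factor to SPPB change. This also stands, and it is why the size is given as a range starting at zero.

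Third, the effect is modest and in the safe direction. At q of 0.05 to 0.10 it is 1 to 3 points of power, and power without the factors stays near 79% to 80% throughout. The simulation therefore does not show the trial falling short of its target because of this omission.

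What the objection does not remove is that the article does set out the primary comparison, mentions multi-covariate modelling only as exploratory work, and never links the stratified design to the analysis. Adding the factors costs 0.1 point of analytic power if they are irrelevant and helps if they are not, so there is little reason to leave the matter open.

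**Conclusion.** The point holds in a limited form. The trial randomises within groups that its stated primary model does not mention. If the three factors predict SPPB change beyond baseline, omitting them gives a conservative test and over-wide intervals: adjustment would narrow the interval by about 2.5%, 5% and 10.5% at assumed partial R² of 0.05, 0.10 and 0.20, with the type I error and power figures shown above. If they do not, nothing is lost. These sizes rest on the assumed block size, prevalences and baseline correlation as well as on partial R². The direction does not depend on the particular values chosen.

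Two stronger readings should be avoided. The omission does not bias the treatment estimate or inflate false positives, so a positive result would not be undermined by it. And it is not established that power is being wasted, because that needs a prognostic strength which the documents do not supply. This is an inexpensive improvement to make before analysis, not a demonstrated error.

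**What to change.** Replace the ANCOVA sentence with an explicit model: SPPB change from baseline to t3 (or SPPB at t3) = arm + baseline SPPB + conditioning intensity (reduced-intensity or myeloablative) + haploidentical transplantation (yes or no) + type of GvHD (acute or chronic). Enter the three factors as main effects, not as eight strata, since some strata may be very small. If the full protocol or analysis plan already specifies this, the authors need only confirm it.

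The cost is one sentence and three of 81 residual degrees of freedom. The factor values are already recorded for randomisation, so no new data are needed. Fixing the covariates before analysis also removes a choice that would otherwise be open in an unblinded trial. Using the same factors for secondary outcomes, each with its own baseline value, would be consistent but is optional.

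### Adverse events are to be evaluated in an undefined per-protocol population, so events in patients who stop exercising are liable to drop out of the safety table

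*Protocol article*

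**What the plan says.** The section on the intended statistical analysis uses two populations. For efficacy: "The primary analysis will be based on an intention-to-treat principle". For safety: "Adverse events will be evaluated descriptively based on the per-protocol population". The article does not say what makes a patient per-protocol. It gives no attendance or completion threshold and mentions no other population for adverse events.

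The Safety section sets out how long events are monitored: "Adverse event monitoring will begin after participants have been randomized and will last 24 weeks". As to which events count, it says: "All adverse events related to the intervention will be recorded and reported according to the standardized guidelines for reportable events". It adds that patients "will be advised to stop exercising when they feel pain or other symptoms". According to the Interventions section, the choice to end training or nutritional support for one patient "will be made jointly within the investigator team if there is concern that the intervention is causing harm". Under Exercise intervention, the article lists symptoms and clinical findings for which sessions are temporarily interrupted. Table 1 lists adherence for the exercise programme, in the intervention arm only. The data collection section ends data collection when a patient withdraws from the study.

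**The concern.** A per-protocol set, as the term is normally used, keeps patients who completed or adhered to the assigned intervention. Where an adverse event can itself cause non-adherence, choosing the safety set on adherence selects on the outcome being described. A patient whose training is stopped because it is thought to be harmful is the one the safety table most needs, and is also a likely exclusion.

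The arms may be affected unequally. Falling short on exercise can happen only in the experimental arm, so any exclusion for that reason falls there and the comparison of event frequencies is no longer between the groups as randomised.

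The safety result will carry weight. The article presents the trial as the first randomised trial focused on GvHD patients, and the background says there is no evidence on structured exercise in this group. No data monitoring committee and no periodic benefit-risk assessment are planned. The descriptive adverse event evaluation is the only safety analysis that the article describes.

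**Working it through.** **1. The passages side by side**

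| Step | Where | What follows |
|---|---|---|
| Monitoring starts at randomisation | Safety | Related events before stopping are recorded |
| Suspected harm can end an individual's intervention | Interventions | Harm can lead to non-completion |
| Symptoms and clinical findings interrupt sessions; patients are advised to stop on symptoms | Exercise intervention; Safety | Harm can lead to missed training |
| Exercise adherence recorded in the intervention arm only | Table 1 | Exclusion for poor exercise adherence can occur in one arm only |
| Adverse events evaluated per-protocol | Intended statistical analysis | Recorded events of excluded patients leave the evaluation |

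The first three rows link events to non-adherence. The last row links non-adherence to absence from the table, provided that per-protocol has its usual meaning.

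**2. The plan's own figure**

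The Sample size section requires 42 per group and allows for losses: "we expect a drop-out rate of 15% and a mortality rate of 10"%. Then 42 / (1 − 0.15 − 0.10) = 42 / 0.75 = 56 per group, or 112 in total, as stated. The allowance is 56 − 42 = 14 per group, 28 in total. It covers loss to the primary endpoint assessment. It is not a count of per-protocol exclusions, and the article gives no such count.

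**3. Illustration of the mechanism (risks assumed, not from the document)**

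Suppose, for illustration only, that 42 of 56 patients in an arm are kept and 14 excluded. Let p_k be the event risk in kept patients and p_e the risk in excluded patients. The per-protocol table shows p_k. The risk in all randomised patients is

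(42 × p_k + 14 × p_e) / 56 = 0.75 × p_k + 0.25 × p_e.

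| p_k | p_e | All randomised | Per-protocol | Ratio per-protocol / all |
|---|---|---|---|---|
| 10% | 5% | 7.5 + 1.25 = 8.75% | 10% | 1.14 |
| 10% | 10% | 7.5 + 2.5 = 10.0% | 10% | 1.00 |
| 10% | 20% | 7.5 + 5.0 = 12.5% | 10% | 0.80 |
| 10% | 30% | 7.5 + 7.5 = 15.0% | 10% | 0.67 |
| 10% | 50% | 7.5 + 12.5 = 20.0% | 10% | 0.50 |
| 5% | 50% | 3.75 + 12.5 = 16.25% | 5% | 0.31 |

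The result depends wholly on how p_e compares with p_k. Equal risks give no bias. A lower risk in excluded patients would reverse it. The document's rules on stopping make a higher p_e the likelier case in the experimental arm, but supply no value for it.

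**The case against.** The strongest reply is that per-protocol is undefined. Reducing load, interrupting sessions and stopping for suspected harm are all written into the protocol, so a patient managed that way could be said to have followed it and might be kept. This stands to the extent that exclusion is plausible rather than stated. A reader might infer that the safety conclusion will certainly be biased towards harmlessness; the document does not support that certainty. The reply does not rescue the sentence, though. If everyone who started is meant, per-protocol is the wrong name for that set and the wording still needs correcting.

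A reader might also take the plan's figures to show that 28 of 112 patients leave the safety table and that harm is understated by a third to a half. Neither follows. The 28 is attrition assumed for the primary endpoint, and the risks that give those fractions are assumptions. Patients who stop early also have less exposure, so a lower risk of related events among them is possible.

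Nor should infections, GvHD flares or deaths in general be counted as lost through this sentence. The Safety section commits to recording events related to the intervention. An event judged unrelated may be missing from any population, and that is a separate matter.

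Finally, related events are to be recorded and reported from randomisation without a per-protocol restriction, reasons for drop-out are recorded where possible, and adverse events carry no hypothesis test. All true. These points limit the damage to the evaluation at the end of the study, but that evaluation is what readers will rely on.

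**Conclusion.** The point holds as a stated choice of population that is wrong for its purpose. It is not a detail left to an unseen analysis plan, because the article names the population. As written, events recorded before a patient stops are liable to be left out, harm in the experimental arm may be understated, and the comparison between arms may be distorted.

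The direction rests on two things: the usual meaning of per-protocol, and the document's own rules tying suspected harm and symptoms to stopping or interrupting exercise. The size cannot be derived from the document. The primary SPPB analysis is unaffected.

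**What to change.** Replace the sentence on adverse events with: *Adverse events are summarised descriptively for all randomised patients, by allocated arm, regardless of adherence or completion, including every event recorded up to withdrawal.* Add a supportive tabulation by intervention actually received, and a listing of recorded events that led to discontinuation of the intervention. A per-protocol summary may stay as a supplement at most, and then the set needs a definition.

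The cost is a few lines in the analysis section. It needs no extra patients, visits or data, because the events concerned are already to be recorded from randomisation. A listing of all deaths is not part of this change: it goes beyond the commitment to record related events and would need data after withdrawal, which the article says are not collected.
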